## Abstract

**Background:**

Despite the known benefits of early, specialized intervention for toddlers with Autism Spectrum Disorder (ASD), access to such intervention remains limited. This pragmatic trial examines a novel healthcare delivery model (Screen-Refer-Treat [SRT]), which capitalizes upon existing health care and early intervention (EI) infrastructure to increase community capacity for ASD detection and treatment before age 3, when it is likely to have the greatest impact. This model comprises three components: (1) universal use of Stage 1 ASD screening by primary care providers (PCPs) at 18-month well-child visits (i.e., Screen); (2) immediate referral of positive screens to a community-based EI program (i.e., Refer); and (3) provision of an inexpensive, evidence-based ASD-specialized treatment by EI providers, after verifying ASD risk with a Stage 2 screen (i.e., Treat). This paper describes our research design and the initial successes, challenges, and adaptations made during the early implementation phase.

**Method/design:**

A stepped-wedge cluster RCT was used to implement the SRT model sequentially in four diverse Washington State counties (“clusters”). Counties are randomly assigned to the time of receipt of the SRT intervention, which comprises training workshops and technical assistance focused on the use of evidence-based ASD screening and intervention tools. Separate cohorts of families with toddlers (16–35 months old) with and without ASD concerns are recruited before and after the SRT intervention from participating PCP practices and EI programs. PCPs and EI providers complete measures on their screening, referral, and intervention practices before and after the SRT intervention. Each family cohort completes surveys about their well-being, parenting efficacy, health care satisfaction, and toddler’s social-communicative behaviors.

**Conclusion:**

This trial is the first of its kind to work simultaneously with two service delivery systems with the goal of improving early detection and treatment for ASD. Our approach was successful in attaining buy-in from PCPs and EI providers, building and maintaining partnerships with providers, and achieving high levels of retention and survey completion. Fostering provider engagement and problem-solving issues together as partners were integral to overcoming the main challenges. Numerous lessons have been learned thus far, which have applicability for implementation researchers in ASD and those in other fields.

**Trial registration:**

The registration number for this trial is NCT02409303 and it was posted on ClinicalTrials.gov on April 6, 2015.

## Background

Autism Spectrum Disorder (ASD) is a complex neurodevelopmental disorder characterized by severe impairment in two broad domains: social communication and behavioral rigidity [1]. The prevalence of ASD has increased steadily over the years and is now estimated to affect 1 in 59 children in the United States (U.S.), with children from Hispanic backgrounds identified at lower rates and later ages due to inadequate detection [2]. Although there is currently no known cure for ASD, early identification and specialized intervention have led to significant improvements in social, language, cognitive, and behavioral functioning [3–7]. To promote early detection and optimize child outcomes, the American Academy of Pediatrics (AAP) published ASD practice guidelines that include conducting universal ASD-specific screening with a standardized tool at 18 and 24 months of age [8]. However, guideline compliance is low [9], with primary care providers (PCPs) reporting numerous barriers to screening, including insufficient time during well-child visits, work flow challenges, and reimbursement issues [10–13].

The prevalent model for ASD care requires a formal diagnosis from a qualified professional to obtain access to ASD-specialized intervention. Most communities have insufficient numbers of professionals with expertise in diagnosing or treating ASD; thus, many toddlers with ASD fail to receive appropriately specialized intervention during the birth-to-three years, when its impact might be greatest [14, 15]. Concerned parents may encounter delays of up to 2 years before receiving an ASD diagnosis and/or specialized services [16–18]. This service vacuum not only creates stress for concerned parents, but also provides a disincentive for PCPs to conduct early ASD screening [9, 16, 19]. In this paper, we describe an alternative service delivery model and a pragmatic trial we are conducting to evaluate the model.

### Designing a new service delivery model for ASD: the screen-refer-treat model

The Screen-Refer-Treat (SRT) model employs state-of-the-art developments in ASD detection and intervention and capitalizes on a readily accessible service delivery infrastructure [20]. The goal of the SRT model is to use a preventive intervention approach and mitigate emerging ASD behaviors during a critical period of development. This model introduces a significant shift in the conceptualization and implementation of ASD services by: (1) offering an ASD-specialized intervention to toddlers when ASD is first *suspected*, rather than waiting until a formal ASD diagnosis is conferred; (2) involving *two integral and interrelated parts of the service delivery system—*primary care and early intervention (EI)—to increase care coordination (See Fig. 1); and (3) addressing obstacles associated with early detection and intervention through the *use of technology* to expedite screening. Two stages of screening are used: Stage 1 (designed for primary care settings), and Stage 2 (designed for referral settings) [21].

The SRT model comprises three components: PCPs conduct universal Stage 1 ASD screening at the 18-month well-child visit (Screen); PCPs immediately refer toddlers who screen positive to a community-based EI program (Refer); and EI providers initiate ASD treatment (Treat) after verifying ASD risk with a Stage 2 screen.

#### Screen

PCPs screen children at 18-month well-child checks using the Modified Checklist for Autism in Toddlers-Revised, with Follow Up (M-CHAT-R/F) [22, 23]. The M-CHAT-R/F is a well-validated Stage 1 parent-report screening tool for detecting ASD in population-based settings. It comprises two components: a 20-item behavior checklist completed by parents; and follow-up questions conducted as an interview if the child screens positive on the checklist. In typical clinical practice, however, time constraints often prevent PCPs from administering the follow-up interview questions [9, 10], which can lead to elevated rates of false positive results [22, 24]. To circumvent this challenge, we developed a web-based version of the M-CHAT-R/F [25, 26] that automatically triggers the appropriate follow-up questions for parents to complete if the checklist score indicates that the child is “at risk”. Scoring is automated, and results are delivered electronically to the PCP.

#### Refer

PCPs immediately refer toddlers with a positive M-CHAT-R/F to a community-based EI program. These programs are federally-funded under the Individuals with Disabilities Education Act (IDEA) [27] to serve infants and toddlers under 36 months old who have delays or disabilities, and are available in all communities at no cost to families.

#### Treat

EI providers assess the need for ASD-specialized treatment using the Screening Tool for Autism in Toddlers (STAT) [28–30], a 12-item, interactive Stage 2 screen that is completed in 20 min and scored in real time. For children screening positive on the STAT, EI providers deliver an evidence-based, ASD-specialized behavioral intervention, Reciprocal Imitation Training (RIT) [31, 32]. RIT uses a naturalistic behavioral approach and a play-based context to teach imitation skills, which are a core deficit area for young children with ASD. Because imitation is a pivotal skill, RIT has also led to concurrent improvements in broader social-communication skills [31, 32].

### Study aims

This pragmatic trial was designed to test the effectiveness of the SRT model in improving both system-level and family-level outcomes. At the *system level*, our aims are to: (1) increase the number of toddlers receiving ASD screening at their 18-month well-child visit; (2) increase the number of toddlers with positive screens who receive evidence-based behavioral intervention prior to age 3; (3) reduce the length of time between parents’ expressed concerns about ASD and the child’s receipt of ASD-specialized intervention; and (4) reduce disparities in identification of ASD for Hispanic families, given the magnitude of the delays they experience relative to other underrepresented populations [2]. At the *family level*, the SRT project aims to: (1) improve parents’ well-being, parenting efficacy, parenting stress, and health care satisfaction; and (2) improve children’s social-communication skills. This paper describes how the SRT trial was designed and is being conducted, highlighting successes and challenges we have encountered during trial implementation.

## Method

### Study design

The SRT service delivery model was initiated in four underserved counties in geographically distinct areas of Washington (WA) State, using a pragmatic trial framework and a stepped-wedge cluster randomized controlled design (RCT) [33]. The research hub was centralized at the University of Washington, where IRB approval was obtained prior to the commencement of study activities and for all protocol amendments. This paper reports on research activities and data collection that occurred during the first 22 months of this project, prior to implementation of SRT training activities. During this “Pre-SRT” period, two baseline Pre-SRT surveys have been collected from providers, and enrollment of the Pre-SRT cohort of families has been completed.

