#### Stepped-wedge cluster RCT design

After a period of baseline data collection in Year 1, each county (“cluster”) was randomly assigned (using random permutation/shuffling by the biostatistician) to one of four time periods during Year 2 when providers received their training in the SRT components (see Fig. 2). Our decision to employ the stepped-wedge design was based on several considerations. First, early feedback from providers revealed that their motivation to participate over a 5-year study period was contingent on their receipt of the SRT training. Second, this approach removes some of the logistical constraints associated with implementing a complex multi-level healthcare system intervention in multiple locations, by allowing us to stagger training activities for each county. Third, this design allows for concurrent comparisons between counties exposed to the SRT model and those not yet exposed; a simple pre-post comparison may be confounded by policy or system changes occurring between the pre-intervention and post-implementation periods. Randomization was at the county level (cluster) rather than at the organizational level within each county to minimize cross-contamination (i.e., providers already trained in one organization exposing the yet-to-be trained providers in another organization to the SRT components).

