**Fig. 2 Fig2:**
[figure not shown]
Stepped-Wedge Cluster RCT Study Design. The four counties (C1-C4) are randomized to the timing of their SRT training workshops. Lighter shading indicates the period of Pre-SRT family recruitment and data collection, darker shading indicates the Post-SRT family recruitment and data collection window, and black shading indicates the 3-month training and technical assistance (TA) period for providers

Changes in PCP and EI provider practices are examined using a *within-subjects* approach, by comparing service delivery practices before and after SRT intervention. Parent experiences are examined using a *between-subjects* approach, by comparing a sample of parents recruited prior to SRT intervention (Pre-SRT cohort) to a separate sample of parents recruited after SRT intervention (Post-SRT cohort); parents were not aware of the study design and, as such, did not know what cohort they were in.

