#### Patient-level services data

We encountered significant obstacles to the completion of the PCP Checklist and EI Checklists, which were developed to collect information on the services delivered to individual children. While we anticipated that 1120 PCP checklists would be completed by PCPs during the first 6 months of data collection, that milestone was not met until 12 months into the study. Feedback revealed that the PCP Checklist procedure was not well integrated into their office work flow; as a result, strategies for modifying their work flow were developed through consultation with the office manager and PCPs. In addition, checklist completion goals were established for each practice, and incentivized with: (1) their choice of materials for their practice (e.g., books or toys for their waiting area), and (2) performance feedback in the form of run charts, enabling them to compare their checklist completion rates with other (anonymized) practices. We also met with challenges obtaining EI Checklists, as it was difficult for EI programs to identify staff members who had the time and knowledge to provide the requested information. Of the 85 families enrolled in EI, only 54 checklists (64%) were completed. In addition, considerable delays in returning the EI Checklists rendered it difficult to compare parent and provider reports of services delivered.

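### Read plainly, both Pre-SRT provider surveys and Pre-SRT family enrolment ended before any training, so for these two data streams the wedge does not give the concurrent comparison credited to it, and the stated timings conflict

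*Protocol article*

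**What the plan says.** All references are to the protocol article.

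- **Study design.** The paper covers "the first 22 months of this project, prior to implementation of SRT training activities". In that period, "two baseline Pre-SRT surveys have been collected from providers, and enrollment of the Pre-SRT cohort of families has been completed".
- **Stepped-wedge cluster RCT design.** Each county was randomised "to one of four time periods during Year 2 when providers received their training". One of three reasons for the design is that "this design allows for concurrent comparisons between counties exposed to the SRT model and those not yet exposed". The contrast it is meant to avoid is named: "a simple pre-post comparison may be confounded by policy or system changes occurring between the pre-intervention and post-implementation periods".
- **Text after Fig. 2.** Provider change is assessed within subjects, "by comparing service delivery practices before and after SRT intervention". Parents are assessed by comparing a Pre-SRT cohort with a separate Post-SRT cohort. Training takes a 3-month block in each county.
- **PCP and EI provider measures.** The Practices Survey has two Pre points, at the start of data collection and one month ahead of the provider's own workshop, and three Post points at 6, 12 and 18 months. The PCP Checklist follows every 18-month visit, and no closing date is given.
- **Parent measures.** Surveys recur every three months until the child is 36 months old.
- **Statistical analyses and power.** GLMMs are planned. The provider power figures are for Pre versus Post differences.

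**The concern.** A stepped wedge guards against secular change only if some clusters are still untrained, and still measured, after others have been trained. The Study design section describes two data streams for which this does not happen: the last Pre-SRT provider survey and the last Pre-SRT family enrolment both fall before the first training. Every Pre observation in those streams is then earlier in calendar time than every Post observation, and a change in policy or services between the two periods would count as an effect of SRT. That is the confounding the article says the design addresses. A calendar-period term in the analysis plan could not repair it, because the necessary observations would not exist.

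The timing statements also disagree. Second surveys tied to staggered workshops cannot all precede the first workshop by more than the stagger allows. Four training periods in Year 2 do not fit 22 months without training.

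**Working it through.** **1. Which contrast was powered.** Inputs from Statistical analyses and power: 40 PCPs, 50% baseline, 22 points, 80% power. Alpha is not stated; 0.05 two-sided is assumed. A one-sample test gives

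power = Φ[(0.22 − 1.96·√(0.25/40)) / √(0.72·0.28/40)] = Φ[(0.220 − 0.155)/0.071] = 0.82.

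The detectable difference at 80% power is 21.6 points, so the stated figure is reproduced. Two independent groups of 40 would give power of 0.52. For 80 EI providers and 15 points (baseline not stated, 50% assumed) the same formula gives 0.78. The figures therefore match a single-group before-after calculation with no step or period term. This shows how the study was sized. It does not fix the analysis model.

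**2. Can exposure be separated from calendar time?** Assumption: training starts at months 0, 3, 6 and 9, counted from the first county's training (3-month steps, taken from the 3-month block). Fit county effects and calendar-quarter effects, then add a column for whether the county is trained. If the rank does not rise, the effect cannot be estimated separately from period.

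| Data stream and schedule | Last Pre | First Post | Rank without / with exposure |
|---|---|---|---|
| Provider surveys, Study design section read plainly | −1 | +6 | 13 / 13 |
| Provider surveys, second survey one month before own workshop | +8 (fourth county) | +6 (first county) | 15 / 16 |
| Family entry data, enrolment closed before training | quarter starting −3 | quarter starting +3 | 12 / 12 |
| Family data, adding quarterly follow-up in untrained counties | quarter starting +6 | quarter starting +3 | 13 / 14 |

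On the plain reading the first and third rows are not identifiable. The second row is identifiable through one overlapping quarter only. The fourth is identifiable through two quarters.

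**3. Is there follow-up to provide that overlap?** From Table 5, mean time from entry to 36 months of age is 36 − 27.63 = 8.4 months (ASD Concerns), 36 − 23.28 = 12.7 (DD Concerns) and 36 − 20.56 = 15.4 (No Concerns). The assumed span from first to last county training is 9 months. Some Pre-SRT families in late counties could still be answering surveys after early counties were trained.

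**4. Do the completed surveys cover all counties?** Provider and parent surveys reports that 44 of 58 PCPs and 76 of 87 EI providers completed both Pre surveys. From Table 4:

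- Without Yakima, at most 58 − 19 = 39 PCPs could have done so, fewer than 44.
- Without Skagit, at most 58 − 16 = 42, fewer than 44.
- Without Spokane, at most 87 − 60 = 27 EI providers, fewer than 76.
- Without Lewis, 58 − 14 = 44 and 87 − 11 = 76, exactly the reported totals.

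So at least three counties had second surveys in hand. Under the assumed steps, workshop-timed second surveys would fall at months −1, 2, 5 and 8, and only one of these precedes the first training. Lewis cannot be settled from these totals.

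**5. Year 2.** Four 3-month blocks in months 13 to 24 start at about months 13, 16, 19 and 22. A project with no training in its first 22 months cannot also have held the first three, unless the two statements use different clocks.

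**6. Cost of period effects.** In an idealised wedge of 4 counties and 5 periods with county effects, the exposure sum of squares is 5·(0.8·0.2 + 0.6·0.4 + 0.4·0.6 + 0.2·0.8) = 4.0 without period effects and 5 − 1 − 2.5 = 1.5 with them (total minus county minus period). The variance ratio is 4.0/1.5 = 2.67 and the standard error ratio is √2.67 = 1.63. For the five workshop-timed provider surveys the corresponding values are 4 × 5 × 0.6 × 0.4 = 4.8 and 0.30, a standard error ratio of √(4.8/0.30) = 4.0.

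**The case against.** The strongest reply is that the Study design section does not speak county by county, and that workshop-timed second surveys would restore an overlap. The county schedule is in Fig. 2, which is not shown here. The article also leaves model terms to an analysis plan that may contain a period effect. Concurrent comparison was one of three reasons for the design; provider motivation and staggered logistics are unaffected. The Discussion already says that inference will be cautious and the analysis not treated as confirmatory.

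Much of this stands, and it rules out several stronger readings that a reader might infer:

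- *That all Pre-SRT data collection had closed.* Only two provider surveys and family enrolment are reported complete. Parent follow-up continues, and the PCP Checklist has no stated end.
- *That closure in all four counties before any training is established.* It is the plain reading, but it is an inference, and the survey totals are also compatible with Lewis having no second survey.
- *That the randomised order contributes nothing.* Follow-up and checklists in untrained counties can make the effect identifiable.
- *That the analysis has no calendar term.* The article is silent, and silence on a model term is not an error here.
- *That drift in outcomes has been shown.* The immigration-policy remark concerns participation. The checklist measures ("checklist completion goals were established for each practice, and incentivized") concern return of forms, not screening or referral. No drift rate is given, so no size of bias can be stated.
- *That Year 2 against 22 months is a plain error.* The reported delay of about a year in starting data collection may explain it.

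What the reply does not remove is that, on the schedule as written, a period term cannot rescue provider surveys or family entry data.

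**Conclusion.** The point holds in limited form, at moderate severity. Read plainly, the Study design section places the end of both Pre-SRT provider surveys and Pre-SRT family enrolment before training began. For those two streams the design then lacks the concurrent comparison claimed for it, and exposure is inseparable from calendar period. The section also conflicts with workshop-timed second surveys, and with Year 2 training unless the start-up delay moved the calendar. For other outcomes concurrent controls may exist.

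This rests on the plain reading of the Study design section, on 3-month steps between counties, and on quarterly calendar periods. The size is a matter of identifiability: no separate estimate on the plain reading, and a thin one (a single overlapping quarter) for provider surveys on the workshop-timed schedule. The amount of bias is unknown.

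**What to change.** 1. Reconcile Study design, Stepped-wedge cluster RCT design, and PCP and EI provider measures by giving, for each county, the training date, the date of the second provider survey and the closing date of Pre-SRT enrolment. State which clock Year 2 and the 22 months use. Cost: a short table.
2. Until each county's own training, continue the PCP Checklist and existing parent follow-up there, both already planned. Take the second provider survey one month before that county's workshop, as the measures section states. If it was taken earlier, a repeat wave at $20 per provider costs at most (58 + 87) × $20 = $2,900 in survey payments.
3. In the GLMMs, code exposure as whether the county is trained at the measurement date, and add calendar-period effects. Cost: wider intervals, with a standard error about 1.6 times larger in the idealised wedge and more where the overlap is thin.
4. For any outcome with no untrained county measured after the first training, withdraw the concurrent-comparison claim and report an uncontrolled before-after estimate. Cost: wording, and a weaker claim.

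Reopening Pre-SRT family enrolment is not asked for; given the recruitment difficulties reported in the Discussion it would not be cheap.
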